#### RCT primary outcome measure

The primary outcome measure for the RCT is work-status. Work-status is defined as sick leave and RTW. In this study, the following indicators are measured:

1) Time to partial and to full RTW, meaning number of calendar days between end of maternity leave and first day at work

2) Time to full RTW corrected for partial RTW

3) Partial and full RTW rate at 12, 24 and 52 weeks follow-up

4) Incidence of sick leave in the first year after delivery, following full RTW

5) Time to first recurrent sick leave in the first year after delivery, following full RTW

6) Total days of sick leave in the first year after delivery

7) Frequency of sick leave periods in the first year after delivery

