## Background

Many women experience health problems during the first year after childbirth [1-4]. Common postpartum problems are fatigue, bowel problems, lack of sleep, postpartum depression, urinary incontinence, back pain and pelvic pain [1,4-6]. These common physical and mental health problems can lead to sick leave and long-term sickness absence from work [1].

In The Netherlands, every pregnant employee has the right to receive paid maternity leave, also called pregnancy and delivery leave. The total duration of this leave is 16 weeks, divided over four to six weeks before the delivery term and 10–12 weeks thereafter. About 90% of Dutch working women had the intention to return-to-work (RTW) after the birth of their first child [7]. A Dutch study described that 29% of working women were absent due to sickness for two weeks or more after maternity leave [1]. Sick leave postpartum was often long-term; in 55% of cases the sickness absence exceeded 12 weeks. The most occurring causes of sick leave postpartum were: pelvic pain (30%), back pain (26%), fatigue (23%), and mental problems (14%). [1]. Despite an abundance of literature about regular RTW and sick leave, little is known about the process of RTW after childbirth. A broad range of factors may contribute to RTW or sick leave, for instance factors like breastfeeding, childcare, social support, work load, distress, health, lack of sleep or health complaints. Therefore, it is important to gain insight into which factors hinder RTW after the end of maternity leave, as well as into the prognostic factors which lead to the development of these complaints.

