A structural contact between supervisors and women on maternity leave, supported by early medical advice of occupational physicians during maternity leave may increase the chances of RTW after maternity leave or reduce the incidence of sick leave after maternity leave. This paper describes the design of the Mom@Work study, a randomised controlled trial (RCT) and cohort study, conducted at Body@Work, Research Centre Physical Activity, Work and Health, TNO-VUmc in Amsterdam, The Netherlands. The Mom@Work study has three aims. The first aim is to investigate the effectiveness and cost-effectiveness of an early intervention in reducing sick leave in women after maternity leave in a randomised clinical trial. Our hypothesis is that supervisors who have structural contact with their employees during maternity leave combined with occupational health care, when needed, will be more effective in reducing the number of sick leave days after maternity leave than supervisors who do not. The second aim of the study is to examine which factors contribute to RTW for women after childbirth. The third aim is to examine which factors contribute to the development of the following postpartum complaints: pregnancy-related pelvic girdle pain, depression and fatigue. The second and third aim are examined in the cohort study.

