### Sample size

Van Beukering found that in 2002 about 30% of the women were taking sick leave after the maternity leave has ended[1]. In the Mom@Work study a decrease of 10% in sick leave at the end of the maternity leave to 20% (30–10 = 20%) is expected in the intervention group. To detect this 10% difference in sick leave, a minimum of 275 women is required per group. This difference can be detected with a power (1-β) of 80% at α= 0.05. A total of at least 550 women is needed for the entire study.

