### Analysis

For the RCT, data will be analysed using statistical tests such as linear regression analysis and Cox regression analysis. The dependency of the observations will be taken into account by performing a multilevel analysis. The multilevel analysis will be performed with a four-level data structure where time, participants, supervisors and companies will be defined as levels 1, 2, 3 and 4, respectively. The analyses will be adjusted for baseline and prognostic dissimilarities, if necessary. Both an intention-to-treat analysis and a per-protocol analysis will be performed. For the cohort study, multilevel analysis will be performed with a three-level data structure where time will be defined as level 1; participants, level 2; and the companies, level 3.

The economic evaluation, which will be performed from a societal perspective, will consist of an analysis of differences in the total, direct and productivity loss costs between the intervention and control group, as well as a cost-effectiveness and cost-utility analysis of the intervention compared to common practice. In the cost-effectiveness analysis, sick leave will be the effect measure and the total costs will comprise all costs except those of productivity loss. Utilities will be based on the Euroqol questionnaire [19]. Quality Adjusted Life Years (QALY) will be calculated by multiplying the utility with the amount of time a patient spends in this particular health state. Incremental costs per QALY gained will be calculated applying both Dutch and UK tariffs. Bootstrapping methods will be used to estimate 95% confidence intervals for the incremental cost-effectiveness ratios and to derive cost-effectiveness planes and acceptability curves.

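### Hypothesis, primary outcome list and sample size point to different endpoints, so the stated 80% power attaches to no listed primary outcome and the deciding result is not uniquely defined

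*Protocol article*

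**What the plan says.** Three sections of the protocol article bear on what the trial is meant to show.

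- **Background (hypothesis).** Supervisors who make the structural contact "will be more effective in reducing the number of sick leave days after maternity leave than supervisors who do not". The quantity is a count of days.
- **RCT primary outcome measure.** "The primary outcome measure for the RCT is work-status. Work-status is defined as sick leave and RTW". Then comes "In this study, the following indicators are measured", followed by seven numbered items with no order of importance. The first is "Time to partial and to full RTW, meaning number of calendar days between end of maternity leave and first day at work" and the third is "Partial and full RTW rate at 12, 24 and 52 weeks follow-up". The others are full RTW time corrected for partial RTW, sick leave incidence after full RTW, time to first recurrence after full RTW, total sick leave days in the year from delivery, and number of sick leave periods in that year. The abstract likewise gives the primary outcomes in the plural.
- **Sample size.** The trial expects "a decrease of 10% in sick leave at the end of the maternity leave to 20" percent, from 30%, and concludes that 275 women per group (550 in all) give 80% power at α = 0.05. The quantity is a yes/no status at one time.

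The Analysis section says "data will be analysed using statistical tests such as linear regression analysis and Cox regression analysis", within a multilevel structure, and names no lead indicator.

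**The concern.** The primary outcome, the hypothesis and the sample size should describe the same comparison. Here the powered comparison is not on the primary list, the hypothesised one is on the list without priority, and the list has no leader. Two things follow.

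1. The 80% power cannot be read as the trial's chance of a positive primary result, because none of the listed primary outcomes is the one it was computed for.
2. When results arrive, indicators may disagree. For example, RTW may differ at 12 weeks but not at 52, or incidence may differ while total days do not. The article gives no basis for saying which result is the primary one.

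This is not detail normally deferred to an analysis plan. All three statements are in the article, and no later document can put the powered endpoint on the article's primary list.

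**Working it through.** **1. The plan's own figure.** Inputs from Sample size: 30% v 20%, power 80%, α = 0.05. Allocation is 1:1 (blocks of four, Group allocation). Sidedness is not stated; two-sided is assumed.

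n per group = [1.960·√(2·0.25·0.75) + 0.842·√(0.30·0.70 + 0.20·0.80)]² / 0.10² = (1.200 + 0.512)² / 0.01 = 293.2, so 294.

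The unpooled and arcsine formulas give 291 and 292, and the continuity-corrected one 313. One-sided variants give 229-231, or 251 with correction. None gives 275. Power at 275 per group, two-sided:

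Φ[(0.10·√275 − 1.200) / 0.608] = Φ(0.753) = 77.4%.

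One-sided it is 85.8%. Neither figure allows for clustering by supervisor.

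**2. Counting the primary list.**

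| Indicator | Comparisons |
|---|---|
| 1: time to partial, time to full RTW | 2 |
| 2: corrected time to full RTW | 1 |
| 3: partial and full RTW × three times | 6 |
| 4 to 7: one each | 4 |
| Total | 13 |

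**3. Matching the other two endpoints to the list.**

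- *Powered endpoint (on sick leave when leave ends).* The nearest item is the full RTW rate at 12 weeks, since postpartum leave lasts 10-12 weeks. It is not the same: the Discussion notes that some women extend leave by vacation, unpaid or parental leave for up to three months, so not having returned does not mean being sick. Indicator 1 starts at the right moment but measures time to return. Indicator 4 counts sick leave only after full return, so it misses an absence that begins when leave ends.
- *Hypothesised endpoint (sick leave days after leave).* Indicator 6 is this quantity, apart from a window that opens at delivery rather than at the end of leave.

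**4. Error if any single indicator could count.** This is conditional, because the article states no such rule. At 0.05 each, independent:

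- 7 tests: 1 − 0.95⁷ = 30.2%
- 13 tests: 1 − 0.95¹³ = 48.7%

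The indicators overlap, and the document gives no correlations. Simulation with assumed equal correlations gives:

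| Correlation | 7 tests | 13 tests |
|---|---|---|
| 0.3 | 27% | 42% |
| 0.5 | 23% | 33% |
| 0.7 | 18% | 24% |
| 0.9 | 11% | 14% |

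If all were kept as primary under Bonferroni, 275 per group would give the 30% v 20% contrast 50.7% power for 7 tests (467 per group needed for 80%) or 42.7% for 13 (521 needed).

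**5. Power if total days were the single primary.** From the document: 30% v 20% with sick leave and 55% of spells over 12 weeks (84 days). The lower limit of 14 days is taken from its planning source: "29% of working women were absent due to sickness for two weeks or more after maternity leave". Assumed: a cap of 287 days (52 weeks less 11 weeks of leave), one spell per woman, and uniform lengths within 14-84 and 84-287 days.

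Mean spell = 0.45·49 + 0.55·185.5 = 124.1 days. Group means = 0.30·124.1 = 37.2 and 0.20·124.1 = 24.8 days; SDs are 72.4 and 61.6. SE = √[(72.4² + 61.6²)/275] = 5.73, so z = 12.4/5.73 = 2.16 and power = Φ(2.16 − 1.96) = 58%. Simulation gives about 57%, and about 56% with truncated exponential spells.

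That assumes the intervention shortens no spell. If intervention spells are 10% shorter, power is about 77-79%; if 20% shorter, about 91-92%. A rank test with no shortening gives about 75-76%.

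**The case against.** The strongest reply is that the seven items are facets of one construct, work-status, and that a protocol article may leave the lead indicator and any multiplicity rule to a document not shown here. Much of this is fair, and it rules out several stronger readings that a reader might draw.

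- *That the false-positive rate is inflated.* This would follow only if any one unadjusted indicator counted as success. No section says so, and an unseen analysis plan may control it. The error figures describe that scenario and are not a property of the plan.
- *That the hypothesis endpoint is absent from the list.* It is there as indicator 6, with a different start of the window. What is missing is its priority.
- *That the named tests rule out the powered yes/no endpoint.* The Analysis section introduces linear and Cox regression as examples, so a binary model is not excluded, and both methods suit other listed indicators.
- *That the trial is badly underpowered for sick leave days.* The figure of about 57% requires that only incidence falls. The Background and Discussion argue that early help prevents long absence, so some shortening is part of the rationale, and modest shortening brings power near or above 80%.

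The choice of endpoint is also open: the hypothesis supports total days as well as the sample size supports end-of-leave status. What the reply does not remove is the conflict among the article's own three statements.

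**Conclusion.** The point stands as an inconsistency that needs correcting. The hypothesis is on sick leave days, the primary list has seven unranked indicators (13 comparisons), and the power calculation is on a yes/no status outside that list. The stated 80% therefore attaches to no listed primary outcome, and the deciding result is not uniquely defined.

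This rests on reading the three sections together and needs no assumption. The sizes do. The 77.4% for the powered endpoint assumes a two-sided test, no clustering and the planning rates as stated; the source figure is for absences of two weeks or more, which is not quite status on the day leave ends. The familywise range of 11-49% applies only under an any-one-wins rule that the article does not contain. Power for total days runs from about 56-58% upward, depending on assumed spell lengths and shortening.

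**What to change.** Designate one primary endpoint before the coded data are unblinded, and bring the hypothesis, outcome list, power statement and model into line with it. Either choice is defensible:

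- **On sick leave, yes/no, at the scheduled end of maternity leave**, derived from the company or OHSP databases already planned as a source. Analyse by intention to treat with a logistic model accounting for supervisor and company. Align the hypothesis sentence. State power as 77.4% two-sided at 275 per group for 30% v 20%, before clustering.
- **Total sick leave days**, as in the hypothesis, with one stated window (from delivery or from the end of leave). Replace the 80% statement with a figure for this endpoint and give its spell-length and spell-shortening assumptions: about 57% if only incidence falls, higher if spells also shorten.

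In both cases list the remaining indicators as secondary in a fixed order and keep the sample size at 550.

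The cost is wording only, with no new data. The sponsor gives up the freedom to claim success on any indicator, and the stated power becomes slightly less favourable for the end-of-leave endpoint, or openly dependent on assumptions for total days.

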### Treatment groups for the RCT

#### Intervention group

The intervention concerns a minimal intervention strategy. The participant receives a phone call from her supervisor six weeks after childbirth and, if needed, support of the occupational health service providers (OHSP). The aim of the intervention is to prevent sick leave by only one phone call and by instigating earlier help by OHSP for the health problems. When health problems are pointed out during the phone call from the supervisor, the women can receive support of the OHSP at least five to seven weeks earlier than usual.

During the structured telephone contact the supervisor uses a standardised interview in the form of a checklist, and asks questions about the women's well being, the child's well being, child care, breast feeding, anticipated work problems, and the expectation of returning to work after maternity leave. When a woman expects that she is not returning to work after maternity leave, or has doubts about it, she is offered support of the OHSP by the supervisor. Only when she wants this support, the OHSP is called in. If requested by the participant, another representative of the company such as another supervisor, executive, line-manager, head of department or HR-advisor initiates this contact.

When a woman does not anticipate any problem with RTW, the supervisor does not offer further support, and he or she only asks when the woman will start working again. Women who do not expect any problem and who do not receive any early help of the OHSP, but who ultimately delay returning to work after maternity leave due to illness, receive the usual sick leave care.

If indicated during the phone call, the supervisor, participant or research team calls the OHSP that the woman needs their support on behalf of the study. A regular, but accelerated procedure for sick leave is initiated by the OHSP. In most cases, an appointment for early medical advice of the occupational physician with the participant is made within one week, instead of the usual six. The OP follows an OHSP complaint specific protocol, if available.

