### Blinding

Given the nature of the intervention, only the control group supervisors and participants are blinded to the intervention. The intervention group supervisors and participants cannot be blinded for the allocated treatment. Furthermore, the researcher and research assistant cannot be blinded for the allocated treatment. However, the data entry assistants are blinded for the allocated treatment. Data on sick leave and RTW are extracted from the routine databases of the company or the OHSP, thus, blinding does not play a role. The data will be blinded for the performance of the analysis. To guarantee blinding of the data for the analysis the participants, supervisors and companies are coded.

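### Indicators 6 and 7 count sick leave from delivery, not from the end of maternity leave, and using routine records does not make blinding irrelevant

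*Protocol article*

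**What the plan says.** The protocol article lists seven indicators of work status under RCT primary outcome measure. Indicator 6 is "Total days of sick leave in the first year after delivery" and indicator 7 is "Frequency of sick leave periods in the first year after delivery". Neither excludes maternity leave. The hypothesis in Background is that the intervention will be "more effective in reducing the number of sick leave days after maternity leave than supervisors who do not".

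Under Intervention group, the supervisor calls six weeks after childbirth. If the woman doubts or does not expect her return and wants support, the OHSP is contacted and told that the request comes from the study. Then "A regular, but accelerated procedure for sick leave is initiated by the OHSP", in most cases with an occupational physician appointment within a week. Under Control group, standard sick-listing follows if the woman cannot return once leave has ended.

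Outcome assessment takes objective sick leave from OHSP databases and, where available, company databases. Blinding says that data on sick leave and return to work "are extracted from the routine databases of the company or the OHSP, thus, blinding does not play a role".

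**The concern.** Two features combine. The counting window of indicators 6 and 7 opens before the period that the hypothesis is about. Inside that extra stretch, the intervention prompts a sick-leave procedure, by design in one arm only, at the organisation that also supplies the outcome data.

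If any such procedure were registered as sick leave before leave ended, the intervention arm would gain days, and possibly periods, that a similar control woman would not. The error would run against the intervention. Indicator 6 is also the indicator closest to the stated hypothesis. Sick leave is the effect measure of the cost-effectiveness analysis as well (Analysis), so the problem would carry over if indicator 6 supplies it.

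The Blinding sentence matters separately, because it tells readers that this route cannot exist.

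**Working it through.** The article gives no figure for sick-leave days per woman, for the share of women referred, or for entries made during leave. There is therefore no planned figure to reproduce. The check compares the passages and then gives a conditional illustration.

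**1. Where each count starts**
- Hypothesis (Background): after maternity leave.
- Sample size: sick leave at the end of maternity leave, 30% versus 20%.
- Indicator 1: "number of calendar days between end of maternity leave and first day at work", so it starts at the end of leave.
- Indicator 4: "Incidence of sick leave in the first year after delivery, following full RTW", so it starts at full return to work. Indicator 5 carries the same restriction.
- Indicators 6 and 7: no start other than delivery.

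Only indicators 6 and 7 are exposed through their window.

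**2. How long the extra stretch is**
- Postpartum leave lasts 10–12 weeks (Background), that is 70–84 of 52 × 7 = 364 days, or 19–23% of the window.
- From the week-6 call to the end of leave: (10 − 6) × 7 = 28 to (12 − 6) × 7 = 42 days.
- From an appointment one week after the call: 21 to 35 days.

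**3. Whether the records are independent of allocation**
- Blinding itself says that intervention supervisors and participants know their allocation.
- The OHSP is told that the request is made for the study, so it can infer the arm.
- These parties can affect whether and when a case is registered.
- Coding participants, supervisors and companies before analysis hides the arm from the analyst. It does not undo a difference that arose when the record was made.

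**4. Conditional size for indicator 6**

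Extra days per intervention woman = f × d. Here f is the share of women referred and logged as sick during leave, and d is the number of days logged before leave ends. The article does not give f; the values below are assumptions.

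| f (assumed) | d = 21–35 (from appointment) | d = 28–42 (from call) |
|---|---|---|
| 0% | 0 | 0 |
| 10% | 2.1–3.5 | 2.8–4.2 |
| 20% | 4.2–7.0 | 5.6–8.4 |
| 30% | 6.3–10.5 | 8.4–12.6 |

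For scale, suppose that the planned 10-point drop works only by preventing whole episodes of mean length L. It then saves 0.10 × L days per woman. The article does not give L. It says only that 55% of absences exceeded 12 weeks, which implies a mean of at least 0.55 × 84 = 46.2 days. The saving is 4.6 days at L = 46.2, 8.4 at L = 84 and 12.0 at L = 120; the last two values of L are assumptions.

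If entries are made during leave, the artefact could be of the same order as the effect. If none are made, it is zero. The documents do not say which.

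**The case against.** The strongest reply is that nothing in the article records sick leave during maternity leave. The sentence after the one on the accelerated procedure explains it as an earlier physician appointment, which is a consultation. The Discussion says that an employee on maternity leave does not have sick-listed status. If that holds for the databases, indicators 6 and 7 already count only sick leave after leave. This stands as a reason to treat the bias as possibly zero. It does not close the point: the Discussion describes ordinary status, and the article does not say how, or from what date, the study-specific procedure is registered.

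The reference to the first year after delivery can also be read as marking the end of follow-up, as it does in indicators 4 and 5. But those two add a restriction on the start, and indicators 6 and 7 do not.

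The arms differ in degree rather than absolutely. Support is called in only if the woman wants it. Control women may call their supervisor or OHSP during leave, and some occupational physicians already ask women with serious pregnancy complaints to make contact before leave ends. This stands and limits the contrast.

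Finally, extraction detail normally belongs in a full protocol or analysis plan. That is correct, and its absence is not the point here. The point rests on a counting window and a blinding claim that the article states.

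**Conclusion.** The point holds in limited form. As worded, indicators 6 and 7 include maternity leave and do not match the hypothesis. Registration can depend on allocation, so the statement that blinding plays no role does not follow from the use of routine records. That second conclusion stands even if nothing is logged during leave.

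The resulting bias against the intervention is a possible risk of unknown size that may be zero. The figures in the illustration rest on an assumed referral share, assumed logging from the call or the appointment, and an assumed episode length.

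A reader might go further and infer that the intervention arm is in fact charged with spurious sick leave, that a definite share of the planned benefit is masked, or that each referral adds a period. The documents do not support these readings. No passage says that the procedure writes a sick-leave entry. Neither a referral rate nor a mean episode length is given. An absence that starts during leave and continues past it is one longer period, not an additional one.

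**What to change.** - Define indicators 6 and 7 as days and periods from the scheduled end of maternity leave to week 52 after delivery, in both arms, whatever date an OHSP file was opened.
- Apply that rule to the coded database extracts by someone blind to allocation.
- Replace the sentence in Blinding with one saying that routine records avoid assessment by the researchers, but that registration may differ by arm because supervisors, participants and the OHSP may know the allocation.
- Use self-reported sick leave, which is already collected, only as a supportive sensitivity analysis. Intervention participants are unblinded, and the questionnaires at weeks 30, 36, 42 and 48 are sent only to women who meet the stated criteria.

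This is a free improvement. It changes the outcome definition and one sentence, uses data and coding already planned, and alters neither the intervention nor the sample size. If nothing is logged during leave, the results do not change.
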